### Study clusters

The study clusters will include SMEs belonging to the Japan Health Insurance Association (JHIA), the largest medical insurer in Japan covering approximately 2.5 million enterprises [25]. The JHIA has 47 branches covering all prefectures across Japan and each branch issues a “health declaration” certificate to enterprises actively working to promote employee health. Certified enterprises are required to appoint a health manager who plans and implements health promotion activities at their workplace. As this intervention will target enterprises with a high degree of readiness for health-promotion activities, we will recruit enterprises with health declarations. In case of multiple locations within a SME, the study cluster will cover only the headquarters and branches on the premises of that location. This is because we assume that the effects of health promotion activities may be smaller for employees in more distant locations compared to those in closer locations within the same or walking distance.

Inclusion criteria for SMEs:In business for more than 3 years.An SME or a branch or business office of an enterprise, with 30–300 employees.Have already entered the Health Declaration conducted by a branch of the JHIA.Both the employer and health manager are aged ≥ 20 years.Facilities for conducting web-based sessions are available in the workplace.The employer’s consent for participation has been obtained.High level of readiness to implement tobacco control measures.

A high level of readiness is defined as follows:The employer is available to participate in sessions: 2–3 sessions (30 min to an hour) during the first 2 months of the intervention.The health manager is available to participate in sessions: once a month for the first 3 months of the intervention and twice a month from the fourth to the sixth month.Health managers can set aside time to implement the measures.

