### Recruitment

The following procedures will be used to register the SMEs for this study: first, we will recruit JHIA branches that agree to cooperate with SMEs’ recruitment by consulting with the headquarters of the JHIA. The recruitment will be conducted sequentially, starting with the branches that have come forward and continuing to recruit additional branches until the target of 36 SMEs has been recruited. Second, we will ask each branch that has offered to cooperate to prepare a list of SMEs that meet the inclusion criteria and mail flyers outlining the study. Third, the research team will organize recruitment briefings for potential SMEs that have responded with interest in this study to clarify the study’s overview and answer any questions they may have. Finally, the employer and health manager of the SMEs that decide to participate will provide written informed consent before the study begins (Supplementary file 2).

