### Sample size and power calculations

The purpose of this study is to test the effectiveness of an intervention that can be disseminated to small- and medium-sized enterprises with limited resources. To achieve this goal, we considered the intervention to be effective if it produces an abstinence rate that is equal to or greater than that in a previous study on similar interventions in a Japanese workplace setting [16]. Thus, we assumed the 7-day point-prevalence abstinence rate to be 13.3% for the intervention group 6 months after the intervention begins.

The smoking cessation percentage of the control group was estimated to be 3.7%. As a breakdown of the 3.7%, the 2.3% under natural behavior change was based on the difference in the average smoking rates between fiscal year 2018 and 2019 for companies belonging to the JHIA (only among companies with 10–999 employees), and the 1.4% as an impact of the revision of the Health Promotion Act was based on the proportion of enterprises that said they would promote tobacco control measures if the Health Promotion Act was revised, according to a survey of approximately 6,000 enterprises nationwide [36]. Thus, we assumed the abstinence rate in the control group would be higher than the 2.5% in the control group who received only information in the previous intervention study. [16]

With a mean of 15 smokers per cluster (assuming 50 employees and a smoking proportion of 30% in each SME) and an intra­class correlation of 0.05 based on a previous cluster randomized study in the workplace [37], which provides a design effect of 1.70, a sample size of 240 smoking employees within 16 clusters per group will be required with a two-sided significance level of 5% and 80% power. Given a 10% loss to follow-up due to unexpected employee turnover, resignation, or retirement, the planned sample size is at least 264 smokers in 18 clusters per group.

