### Statistical analysis

The primary analysis for the primary outcome will be conducted on an intention-to-treat basis, that is all randomized participants who respond as being current smokers at baseline and have the biochemically confirmed 7-day point-prevalence abstinence data at 6 months will be included in the analysis and will be analyzed according to the group to which they were allocated. The primary analysis will exclude the participants lost to follow-up and no imputation of missing data will be performed; however, imputing missing data may be considered to account for all randomized participants in the sensitivity analysis. For the primary outcome, the biochemically confirmed 7-day point-prevalence abstinence rate at 6 months will be compared between the intervention and control groups, and the difference in the abstinence rates with 95% confidence intervals (CIs) will be estimated. A generalized estimating equation (GEEs) method with an identity link and an exchangeable correlation structure will be used. Robust variance will be used for hypothesis testing and estimation. The allocation factors of the number of employees and the implementation of a comprehensive smoke-free policy at the workplace will be adjusted in the GEE model. A two-sided *P* value of 0.05 or less will be considered statistically significant. Because of model convergence issues, we may also consider a logistic regression model with GEEs and an exchangeable correlation structure for hypothesis testing and estimating odds ratios with 95% CIs. Secondary outcomes, including implementation, and process, health, and cost-related outcomes, will also be analyzed. Detailed methods for the secondary outcomes and sensitivity analyses will be specified in the Statistical Analysis Plan before the study data are fixed.

Regarding adherence content, which will be measured in the intervention group only, we will conduct paired t-tests to examine pre- versus post-intervention changes in responses of the adherence measured by the workplace tobacco control checklist.

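### The primary GEE test and confidence interval rest on a robust variance with no named small-sample correction or t reference, although only 36 enterprises are randomised

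*Protocol article*

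**What the plan says.** The Statistical analysis section of the protocol article specifies the primary comparison: a GEE with identity link and exchangeable correlation, adjusted for the two allocation factors (enterprise size and an existing smoke-free policy), tested two-sided at 0.05. On the variance it says only: "Robust variance will be used for hypothesis testing and estimation". A logistic GEE is the fallback if the model does not converge. The same section leaves the detailed methods for secondary outcomes and sensitivity analyses to the SAP. The primary variance is not among the deferred items.

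On the number and size of clusters:
- Recruitment continues "until the target of 36 SMEs has been recruited", randomised 1:1.
- The inclusion criteria in Study clusters admit enterprises "with 30–300 employees", and randomisation is stratified at 100 employees.
- Sample size and power calculations assumes 50 employees and 15 smokers in every enterprise, a control quit rate of 3.7%, and an intraclass "correlation of 0.05 based on a previous cluster randomized study in the workplace".

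**The concern.** The uncorrected sandwich variance estimates its middle term from cluster residuals. With few clusters those residuals are too small, so the standard error is biased downwards. A normal reference then ignores the uncertainty in that estimate. Several features here make both problems worse:
- Intercept, treatment and two covariates are four parameters, all identified only between 36 enterprises.
- The outcome is rare. At 3.7%, 240 analysed controls give 240 x 0.037 = 8.9, or about 9, quitters.
- The eligibility range of 30-300 employees, at 30% smokers, allows roughly 9 to 90 smokers per enterprise.

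At stake are the reported primary P value and interval: an ineffective intervention would be declared effective more often than the stated 5%.

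**Working it through.** **The plan's own figure.** From the sample size section: quit rates 13.3% and 3.7%, 15 smokers per cluster, ICC 0.05, two-sided 5%, 80% power.
- Design effect: 1 + (15 - 1) x 0.05 = 1.70, as stated.
- Unpooled two-proportion formula: (1.960 + 0.842)^2 x (0.133 x 0.867 + 0.037 x 0.963) / 0.096^2 = 128.6 per arm.
- Clusters: 128.6 x 1.70 / 15 = 14.57. Adding one cluster per arm gives 15.57, rounded up to 16, or 16 x 15 = 240 smokers. This matches.
- A t-based power calculation also leads to 16 clusters: 78.4% power with 15 per arm, 81.1% with 16.
- Loss to follow-up: 240 x 1.10 = 264, and 16 / 0.9 = 17.8, rounded up to 18 clusters.

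The planned size therefore reproduces. The question is whether the test holds its level at that size.

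**Simulation of the planned analysis.** From the protocol: 36 clusters, stratified 1:1 allocation, identity link, exchangeable correlation, treatment plus both allocation factors, ICC 0.05, and no true effect at a common rate of 3.7%. Assumed, because the article does not give them: beta-binomial outcome, 40% of enterprises with a smoke-free policy, 15% with 100 or more employees in the equal-size case, the size distributions, and full follow-up. There were 5,000 runs per row (Monte Carlo error about 0.3-0.4 points). The t reference has 36 - 4 = 32 degrees of freedom. KC is Kauermann-Carroll and MD is Mancl-DeRouen.

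| Smokers per cluster | Working variance | Type I error, uncorrected, z | KC, t | MD, t | Coverage of 95% CI, uncorrected, z |
|---|---|---|---|---|---|
| 15, equal | Gaussian | 6.7% | 4.7% | 3.5% | 93.3% |
| mean 15.8, CV 0.40 | Gaussian | 7.2% | 4.8% | 3.7% | 92.8% |
| mean 26.4, CV 0.62 | Gaussian | 7.7% | 5.0% | 3.5% | 92.3% |
| mean 35.0, CV 0.65 | Gaussian | 8.4% | 5.6% | 4.0% | 91.6% |
| 15, equal | binomial | 8.7% | 5.9% | 4.5% | 91.3% |
| mean 15.8, CV 0.40 | binomial | 9.7% | 6.8% | 5.0% | 90.3% |
| mean 26.3, CV 0.62 | binomial | 10.9% | 7.3% | 5.6% | 89.1% |
| mean 35.1, CV 0.65 | binomial | 10.6% | 7.2% | 5.8% | 89.4% |

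The uncorrected standard error is about 6-7% too small with Gaussian and 12-18% too small with binomial working variance. A t reference without a variance correction is not enough: the error is still 6.0-9.4% across these rows.

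**Further runs under other assumptions.**
- Null rates of 3.7% and 8.5%, covering identity-Gaussian, identity-binomial and logit GEE. Equal clusters gave 5.7-7.3% uncorrected. A spread with 6 of 36 enterprises at 100 or more employees (mean 14 smokers, CV 0.78) gave 8.8-11.0%. MD with t gave 3.1-4.6% and 3.3-5.0% respectively. KC with t gave 3.8-5.5% and 5.3-7.3%.
- Identity-link Gaussian model with both allocation factors: 6.9-7.7% uncorrected with equal clusters and 9.3-9.7% with an assumed unequal spread. MD with t gave 3.4-4.8%.

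**Power.** At 13.3% against 3.7%, with 36 equal clusters of 15, full follow-up and Gaussian working variance, power is 91% uncorrected (an inflated test), 87% with KC and t, and 84% with MD and t. The planned 10% loss was not simulated and would lower these somewhat.

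**The case against.** The strongest reply is that the article never says the variance is uncorrected. A Kauermann-Carroll or Mancl-DeRouen sandwich is also a robust variance, the text names neither a normal nor a t reference, and an article often leaves such settings to the full protocol or SAP. This stands in part. A reader might infer that the ordinary sandwich has been chosen, and the wording does not establish that. But the article specifies the primary variance and defers only secondary and sensitivity methods, so an analyst could follow it with an uncorrected software default.

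A reader might also infer that the enterprises are very unequal in size. The documents do not support that either: the eligibility range and the stratification at 100 permit inequality, while planning assumes 50 employees each. The unequal-size figures therefore rest on assumed distributions, two of which have mean cluster sizes (26 and 35) well above the planned 15. The concern survives without them, since equal clusters already exceed 5%.

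Finally, the largest figures for the identity-link model in the table come from a binomial working variance, which the article does not specify. In that setting 8-29% of null runs had fitted rates outside 0-1, which were clipped in the weights; leaving those runs out gives 6.9-9.6%. This limits how firmly the upper end can be stated, but not the direction, which was the same in every setting.

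**Conclusion.** The point holds in a conditional form. As worded, the primary analysis allows an uncorrected robust z-test on 36 enterprises. Such a test would run at about 6-9% under the plan's own equal-size assumption, an excess of roughly 1 to 4 points, and at about 7-11% if sizes vary with an assumed CV of 0.4-0.8. Interval coverage would be about 89-93%. To say flatly that the test runs far above 5% would go beyond the documents, because the size of the excess depends on the working variance and the size distribution, and neither is given. The treatment effect measure, the design and the planned number of enterprises are not in question.

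**What to change.** State in the primary analysis text that the test and confidence interval use the Mancl-DeRouen bias-corrected robust variance with a t reference on clusters minus parameters (32 degrees of freedom with 36 enterprises and four parameters), and that the logistic GEE fallback does the same. Name this one method rather than offering a choice: Kauermann-Carroll with t still reached 7.3% in the unequal-size settings, so it is adequate only if cluster sizes prove similar. A permutation test within the randomisation strata is an optional check. Methods for secondary outcomes can stay with the SAP.

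The cost is one sentence and a software option. Intervals become slightly wider and the test is mildly conservative: type I error was about 3-5% in most settings, and up to 5.8% with binomial working variance and widely spread sizes. With the plan's own effect sizes, power stays above 80% at 36 equal clusters of 15 with full follow-up, so these inputs do not call for more enterprises. Trial status reports that data analysis had not begun at first submission, and the study statistician is to be blinded until the primary analysis. If that is still the case, the sentence can be added without knowledge of the results.

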### Random allocation and adjustment factors for allocation

Each enterprise will be randomly assigned in equal proportion to the intervention or control group using a stratified randomization method of static allocation with two adjusted allocation factors at the workplace level: number of employees (less than 100, 100 or more) and implementation of a comprehensive smoke-free policy on the workplace (yes or no). All employees eligible for the evaluation target (i.e., employees working at the headquarters and branch on the premises of that location) will be allocated to the same group. The workplaces will be randomly allocated by an independent research assistant not involved in the study using computer-generated random numbers prepared in advance by a statistician.

Owing to the nature of the intervention, it will not be possible to blind the assignment of the participants (employers and health managers) and interventionists. They will be informed of their assignment after the baseline assessment is completed. However, the assessor of the biochemical salivary test will be blinded to the randomization groups; the study statistician will also be blinded to the randomization groups until the analysis of primary outcomes at 6-month follow-up is conducted.

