### Outcomes

We will evaluate the health-, implementation-, process-, and cost-related outcomes. Outcome measures, evaluation period, and data sources are summarized in Table 2.

**Table 2 Tab2:** Outcome measures by period and data source

	Baseline	Follow-up		
Outcome measures		6 months	12 months	Data source
Health outcomes				
Smoking status	〇	〇	〇	Employee questionnaire
Cotinine-validated 7-day point-prevalence abstinence rate		〇	〇	Employee questionnaire Biochemical test
30-day point-prevalence of smoking abstinence		〇	〇	Employee questionnaire
Three-month point-prevalence abstinence rate		〇	〇	Employee questionnaire
Six-month point-prevalence abstinence rate			〇	Employee questionnaire
Three months prolonged abstinence rate		〇	〇	Employee questionnaire
Six months prolonged abstinence rate			〇	Employee questionnaire
Proportion of nicotine patches and gum use		〇	〇	Employee questionnaire
Proportion of quit attempts	〇	〇	〇	Employee questionnaire
Number of cigarettes or capsules	〇	〇	〇	Employee questionnaire
Implementation outcomes				
Adoption of two recommended measures	〇	〇	〇	Workplace questionnaire
Penetration of smoking cessation clinic visits		〇	〇	Employee questionnaire
Process outcomes				
Adherence (content) (e.g., Was each recommended measure implemented as planned?)	●	●	●	Workplace tobacco control checklist Interventionists’ notes
Adherence (frequency/duration) (e.g., Were the recommended measures implemented as often and for as long as planned?)		●	●	Health manager’s logbooks Interventionists’ notes
Adherence (coverage) (e.g., What proportion of employees who smoke participated in the cessation campaigns?)		●	●	Health manager’s logbooks Interventionists’ notes
Potential moderators (responsiveness) (e.g., How did employees who smoke engage with the smoking cessation campaigns?)		●	●	Semi-structures interviews Interventionists’ notes
Potential moderators (complexity) (e.g., How complex is the intervention?)		●	●	Semi-structures interviews Interventionists’ notes
Potential moderators (comprehensiveness) (e.g., How specific is the interventions description?)		●	●	Semi-structures interviews Interventionists’ notes
Potential moderators (strategies) (e.g., What strategies were used to support implementation?)		●	●	Semi-structures interviews Health manager’s logbooks Interventionists’ notes

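### The primary GEE adjusts only for two workplace-level allocation factors; adding the smoking items already collected at baseline would be a cheap but small gain in precision

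*Protocol article*

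**What the plan says.** The primary comparison of cotinine-validated abstinence at 6 months is specified in the Statistical analysis section: "A generalized estimating equation (GEEs) method with an identity link and an exchangeable correlation structure will be used", with robust variance. On the covariates of this model it says: "The allocation factors of the number of employees and the implementation of a comprehensive smoke-free policy at the workplace will be adjusted". The section Random allocation and adjustment factors for allocation defines these factors at workplace level: "number of employees (less than 100, 100 or more) and implementation of a comprehensive smoke-free policy on the workplace (yes or no").

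Table 2 (Outcomes) lists "Number of cigarettes or capsules" and "Proportion of quit attempts" with a white circle at baseline, meaning collection in both groups, from the employee questionnaire. No smoker-level variable is named for the primary model.

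Two further statements matter. The plan expects that the identity link may give trouble: "Because of model convergence issues, we may also consider a logistic regression model with GEEs", in which case odds ratios would be reported. What it leaves open is limited: "Detailed methods for the secondary outcomes and sensitivity analyses will be specified in the Statistical Analysis Plan before the study data are fixed". The covariates of the primary model are therefore settled in the article.

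**The concern.** Abstinence is an outcome of the individual smoker, but the only covariates are properties of the employer. Stratifying 36 enterprises on size and smoke-free policy does not directly balance how much their smokers consume or whether they have tried to quit before. If those items predict abstinence, leaving them out has two effects. The variance they could explain stays in the standard error of the one comparison that the trial is powered for. And if the arms happen to differ on them, the estimate is not corrected for that difference. There is little power in reserve, so a gain that needs no new data is worth sizing.

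**Working it through.** **Inputs from the protocol article (Sample size and power calculations):** abstinence 13.3% versus 3.7%, difference 9.6 points; 15 smokers per cluster; ICC 0.05; two-sided 5%, 80% power; 240 smokers in 16 clusters per group, raised to 18 clusters for 10% loss.

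**Reproducing the plan's figure.** Design effect = 1 + (15 − 1) × 0.05 = 1.70. The pooled two-proportion z formula gives 132 per arm; 132 × 1.70 = 224.4, or 15 clusters of 15. With t quantiles on 2 × (16 − 1) = 30 df the same formula gives 238.5, and 238.5 / 15 = 15.9, so 16 clusters and 240 smokers. Adding one cluster per arm to the z result also gives 16. The stated size is reproduced. Power at 240 per arm is 80.2% (t, 30 df).

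**Standard error under the plan.** √[1.70 × (0.133 × 0.867 + 0.037 × 0.963) / 240] = 0.0327, about 3.3 points.

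**Effect of adding covariates.** As an approximation, the variance is multiplied by (1 − R²), where R² is the share of individual outcome variance that the added items explain. The documents give no value, so a range is used:

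| Assumed R² | Fall in SE | Power at 240 per arm |
|---|---|---|
| 0 | – | 80.2% |
| 1% | 0.5% | 80.6% |
| 2% | 1.0% | 81.0% |
| 5% | 2.5% | 82.2% |
| 10% | 5.1% | 84.2% |

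At the mean abstinence of about 8.5%, a prognostic score with an odds ratio per SD of 1.5 gives R² of about 1.3%; 2.0 gives about 4.0%; 3.0 gives about 10%.

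**Simulation.** Assumptions: 18 + 18 enterprises, mean 13.5 analysed smokers, cluster-size CV about 0.6, odds ratios 0.5–0.74 per SD of consumption and 1.5–2.5 for a past quit attempt (30% prevalence), covariate ICC 0.05–0.15. With 6,000 trials per scenario, the ratios of unadjusted to adjusted variance were 1.006 (weak), 1.029 and 1.044 (middle), and 1.074 and 1.109 (strong). These are variance reductions (1 − 1/ratio) of 0.6%, 2.8%, 4.2%, 6.9% and 9.8%. Logit standardisation gave ratios of 1.003–1.08. A separate simulation of the same design found no bias and ratios of about 1.00 (weak), 1.02–1.05 (middle) and 1.07 (strong).

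**Chance imbalance.** With 16 clusters of 15 per arm and an assumed covariate ICC of 0 to 0.10, the SD of the difference in covariate means is √[2 × (1 + 14 × ICC) / 240] = 0.091 to 0.141 covariate SDs. A 1.96-SD imbalance is thus 0.18 to 0.28. Multiplying by √R² × √(0.085 × 0.915) gives a shift in the risk difference of 0.5 points (R² 1%, ICC 0) to 1.7 points (R² 5%, ICC 0.10). In the first simulation the SD of the shift between unadjusted and adjusted estimates was 0.4–1.0 points.

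**Convergence.** Expected quitters are 240 × 0.133 ≈ 32 and 240 × 0.037 ≈ 9. In a small illustrative simulation (250 runs per setting), a binomial-identity GEE failed to converge or gave fitted risks outside 0–1 in about 25–30% of runs with the allocation factors alone, and in about 99–100% with two continuous covariates added. These rates depend on software and covariates. With a constant working variance, the empirical SDs without and with the covariates were 0.0311 and 0.0311, 0.0333 and 0.0327, and 0.0323 and 0.0323.

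**The case against.** The strongest reply is that nothing here is an error. Adjusting for the factors used to stratify is accepted practice, and the robust-variance comparison does not need further covariates to be valid. That stands.

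A reader might infer that imbalance in smoking intensity would bias the primary result. The documents do not support this. Under randomisation such imbalance is random error, and the shifts above are a component of the roughly 3.3-point standard error, not an addition to it. A reader might also take the items to be cigarettes per day and readiness to quit. Table 2 gives no unit for cigarettes or capsules and lists no readiness measure for smokers; the readiness defined under Study clusters belongs to the enterprise.

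The benefit also rests on assumed prognostic strength, and with weak covariates it nearly vanishes. That stands too.

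The convergence objection stands only in part. Adding covariates to a binomial-identity model could trigger the logistic fallback and so change the effect measure. It does not reach a constant-variance identity model or a standardised logit model. The change is nonetheless more than a longer covariate list, because the working variance or estimator has to be specified as well.

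Timing has some weight. The Trial status section reports 12-month evaluation under way in April 2023, so 6-month outcomes exist for at least some enterprises. The same section says analysis had not begun, and the statistician is blinded until the primary analysis.

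Finally, an adjusted supportive analysis may be in the SAP, which is not shown. That would not alter the primary model fixed in the article.

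**Conclusion.** The point holds as a modest efficiency improvement, not as a flaw that threatens the result. The primary model uses no information on the individual smoker although two such items are collected at baseline in both groups. Under assumed prognostic strengths the variance forgone is about 0–1% for weak covariates, 2–5% for middle and 7–10% for strong ones. In plausible cases (R² up to about 5%) that is roughly 0–2 power points on a base of about 80%; about 4 points would need R² near 10%. The second effect is conditional: an unlucky imbalance could move the estimate by about 0.5–1.7 points for R² of 1–5%, against a planned 9.6. All of this rests on odds ratios, covariate ICC and quit-attempt prevalence that the documents do not supply.

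**What to change.** Before unblinding, pre-specify baseline number of cigarettes or capsules and baseline quit attempt (yes/no) as covariates in the primary model, alongside the two allocation factors, and state the unit and look-back period used.

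Keep the risk difference with its 95% confidence interval as the estimate. Obtain it either from an identity link with constant working variance and cluster-robust standard errors, or from a logit GEE standardised to a risk difference. Do not rely on a binomial-identity fit. Fill missing baseline items by simple covariate imputation, which leaves the outcome unimputed as planned. Report the model with the allocation factors only as a sensitivity analysis.

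The cost is a short amendment to the analysis section and SAP, with no new data. The downsides are a changed working variance or estimator, a little covariate imputation, and little or no gain if the items predict poorly. The change must also be dated and documented as made blind, because outcome data are already being collected.
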